# 6. METHODS

## 6.1 Study Design

A double blind placebo controlled phase 1 clinical trial conducted at Danderyds Hospital, Danderyd and Mälarsjukhuset, Eskilstuna both in Sweden.

The double blinded placebo controlled study design has been chosen to enable unbiased assessment of adverse events. The study will be conducted in accordance with the Helsinki declaration on ethical principals for medical research involving human subjects.

Twenty-four volunteers will be included in the study. Following informed consent participants will be requested to donate faeces. Participants will be randomised to treatment group A or B. Treatment will consist of clindamycin 300 mg three times daily for seven days for all. This will be followed by intake of two identical capsules twice daily containing placebo or an autologous faecal mixture for five days. Participants general health and gastrointestinal symptoms will be monitored using questionnaires and stool samples for sequencing of the microbiota will be collected. The study will end when the six month follow up of the last patient ends.

## 6.2 Study population

Healthy non-pregnant volunteers aged 18-40 years.

### 6.2.1 Inclusion criteria:

Written informed consent after meeting with a study physician. Ability to swallow a placebo capsule. Negative pregnancy test and use of adequate contraceptive for women while taking study treatment.

### 6.2.2 Exclusion criteria:

History of disturbed or ongoing bowel condition, delayed gastric emptying syndrome, recurrent aspirations, swallowing dysfunction, antibiotic treatment during the previous 3 months, regular intake of any medication, body mass index <18.5 and >30, any other significant medical history (except resolved traumatic injury). Identification of *C. difficile* in stool sample prior to study start.

## 6.3 Patient screening and patient identification logs

Investigators will keep a record of all patients that are considered for enrolment even if they are not subsequently enrolled in order to verify that the patient population was selected without bias (ICH-GCP 8.3.20). The reasons for non-eligibility are to be defined in terms of one or more of the eligibility criteria.

A screening number will be allocated to each patient after the subject has signed the informed consent in connection with the screening visit. The screening number will allow for the identification of patients irrespective of their possible eligibility for the main study.

## 6.4 RESTRICTIONS

Sexually active males and females of child-producing potential, must use adequate contraception (oral contraceptives, intrauterine device or barrier method of contraception in conjunction with spermicidal jelly or surgical sterile) for the duration of treatment and at least two weeks after completion of chemotherapy. Females of child-bearing potential must have a negative pregnancy test at screening for enrolment.

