## 6.9 Treatment

Participants will come to the Department of Infectious Diseases, Danderyds hospital or Mälarsjukhuset in Eskilstuna the day prior to treatment start to collect clindamycin and for a final briefing. All participants will be requested to take 300 mg clindamycin capsules morning, lunch and evening for seven days. This will be followed by a two and a half day washout period. On day three of the washout period participants will return to Hospital to take the first IMP or placebo dose supervised and to collect their remaining study capsules that are to be stored in a freezer at home. Participants will then be requested to take two study capsules twice daily for a total of five days.

An SMS text message will be sent twice daily to remind volunteers to take the clindamycin and study capsules. Patients and investigators will be blinded as to the content of the capsules. The code will be held by the manufacturers of the capsules that are not involved in the clinical part of the study.

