**Table 1. Outline of study and sampling**

| Days |  | 1 | 1-7 | 8-10 | 10-15 | 16 | 28 | 2 months | 6 months |
| --- | --- | --- | --- | --- | --- | --- | --- | --- | --- |
| Phase | Inclusion | Start | Antibiotic | Washout | Treat | Follow up | | | |
| CRF A | + |  |  |  |  |  |  |  |  |
| *C.diff* screening | + |  |  |  |  |  |  |  |  |
| Faecal sample* | + | + |  | + |  | + | + | + | + |
| CRF B |  | + | + | + | + | + | + | + | + |
| Hospital visit | + | + |  | + |  | + |  |  |  |

*Prior to study start a faecal sample for autologous transplant will be donated.

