## 11.2 Duration

Advertising and recruitment will be done during autumn 2017. The study should start around November/December 2017 and run for 6 months. Sequencing and data analysis will take 6 months. A report should be completed by the end of 2018. Within 90 days of the end of the study the “declaration of end of trial notification” document will be sent to the MPA

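### The only pregnancy test is at screening, nothing limits the time from there to clindamycin, and no repeat is scheduled before first exposure

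*Protocol*

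**What the plan says.** **Pregnancy.** Section 6.4 ties the test to screening: "Females of child-bearing potential must have a negative pregnancy test at screening for enrolment". Section 6.2.1 repeats the requirement without a date: "Negative pregnancy test and use of adequate contraceptive for women while taking study treatment". Table 1 has no pregnancy-test row.

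**Contraception.** Section 6.4 requires it "for the duration of treatment and at least two weeks after completion of chemotherapy", and section 6.2.1 links it to the time on study treatment. Neither covers the interval between screening and treatment.

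**Steps before first dose.** Under section 6.8 stool is donated after inclusion and is then processed, frozen, thawed and encapsulated. Section 6.9 brings participants in "the day prior to treatment start to collect clindamycin and for a final briefing". Section 6.5 places randomisation after eligibility is confirmed and no later than one hour before clindamycin. That is a minimum interval; no maximum appears anywhere.

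**Calendar.** Section 11.2 reads: "Advertising and recruitment will be done during autumn 2017. The study should start around November/December 2017 and run for 6 months".

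**Related criteria.** Section 6.2.2 excludes "antibiotic treatment during the previous 3 months" without saying where the window ends. It also excludes anyone with *C. difficile* found "in stool sample prior to study start"; Table 1 marks that test once, in the Inclusion column. Section 6.4.1 requires medication changes to be asked about at each visit.

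**The concern.** Pregnancy status can change between screening and dosing without the participant knowing. Here the test is fixed at the start of an interval of unstated length, no contraception rule applies during that interval, and no later check is named. The participants are aged 18 to 40, and the exposure is to an antibiotic that they do not need for treatment. A site that follows the text exactly could give clindamycin and capsules to a woman with an undetected pregnancy, in a trial whose population is defined as non-pregnant and whose primary endpoint is safety.

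The antibiotic and *C. difficile* criteria raise a lesser form of the same question. Recent antibiotic use would disturb the baseline stool sample against which recovery of the microbiota is judged. Section 3 also relies on the *C. difficile* screen when it describes the risk of infection as very low.

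**Working it through.** The protocol states no interval from screening to treatment, so there is no figure to reproduce. The check has two parts.

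**1. Is there any point between screening and first dose at which pregnancy must be tested?**

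| Place | What it fixes | Test or limit before clindamycin? |
|---|---|---|
| 6.2.1 | Negative test, undated | No date or interval |
| 6.4 | Negative test at screening | No repeat |
| 6.5 | Eligibility confirmed, then randomisation, at least 1 hour before clindamycin | Names no test; minimum interval only |
| 6.8 | Donation and capsule preparation after inclusion | Adds time; duration not given |
| 6.9 | Drug collection and briefing the day before | No test listed |
| Table 1 | Schedule of procedures | No pregnancy-test row |

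The answer is no. Some gap is unavoidable by design, because the donation follows inclusion.

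**2. How long could the gap be under the protocol's own calendar?**

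Inputs: recruitment in autumn 2017 and start around November/December 2017 (section 11.2). Section 11.2 gives no exact dates. I assume that autumn opens between 1 and 22 September and that first doses fall between 1 November and 31 December.

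Gap = date of first dose − date of screening; months = days / 30.44.

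Worked case: 1 September to 31 December = 30 + 31 + 30 + 30 = 121 days; 121 / 30.44 = 4.0 months.

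| Screened | Dose 1 Nov | Dose 1 Dec | Dose 31 Dec |
|---|---|---|---|
| 1 Sep | 61 days (2.0 months) | 91 (3.0) | 121 (4.0) |
| 22 Sep | 40 (1.3) | 70 (2.3) | 100 (3.3) |
| 1 Oct | 31 (1.0) | 61 (2.0) | 91 (3.0) |
| 1 Nov | 0 | 30 (1.0) | 60 (2.0) |
| 30 Nov | not possible | 1 | 31 (1.0) |

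For the earliest-screened participant the gap is 40 to 91 days if dosing starts between 1 November and 1 December, and 100 to 121 days if it starts on 31 December. For someone screened late it may be a day or a few weeks.

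**The case against.** **Eligibility is confirmed before randomisation.** Section 6.5 randomises only people who meet every inclusion criterion and no exclusion criterion, so a woman known to be pregnant would not be randomised. That stands, and it narrows the point to undetected pregnancy. It does not close the gap: section 6.5 names no test and no date, and a site can satisfy it with the screening result because section 6.4 puts the test there.

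**Section 6.2.1 might mean a negative test during treatment.** The closing words of that criterion more naturally qualify contraception, section 6.4 fixes the test at screening, and Table 1 schedules none later.

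**The inclusion form is not shown.** Its contents cannot be judged, but section 6.10 and Table 1 place its completion at inclusion, so it is not evidence of a later check.

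**The long gap is a constructed extreme.** This is fair. Section 11.2 is a project calendar, recruitment includes advertising, and section 9 shows that approvals were still to come. A reader might infer that participants typically wait 3 to 4 months. The protocol does not support that; the figure is an upper bound under assumed dates. The point does not depend on it, since a gap of weeks is enough for a screening test to miss a pregnancy.

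**Antibiotic use is already re-asked.** A reader might infer that a volunteer who takes an antibiotic after screening remains eligible, or that nothing rechecks medication. The text does not support either. Section 6.4.1 requires a medication history before study start and a question about changes at each visit, and section 6.5 applies the criteria at randomisation. What remains is that the 3-month window has no stated end date and that section 6.4.1 asks only for recording, without a link to eligibility.

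**New *C. difficile* carriage is unlikely to matter much.** Section 1 calls the infection mainly hospital-acquired, and these are healthy young adults. The documents give no basis for material acquisition between test and day 1, so this part is minor.

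**Conclusion.** The point stands for pregnancy. Followed exactly, the protocol tests once, at screening, requires contraception only around treatment, sets no maximum gap and schedules no test before clindamycin. A pregnancy arising or becoming detectable in between can be missed at first exposure.

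The size of the gap is uncertain: from days up to an assumed maximum of 100 to 121 days. That maximum rests on autumn opening between 1 and 22 September and on dosing by 31 December. Because section 11.2 is a plan and not a rule, the calendar itself caps nothing. The probability of an affected participant cannot be estimated from the protocol, and among 24 volunteers it may well be small. The case for acting rests on the avoidable nature of the exposure and the low cost of preventing it.

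The antibiotic window and the age of the *C. difficile* result are minor clarifications. This is protocol content and would not normally be left to a statistical analysis plan.

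**What to change.** **Main change.** Do or repeat the pregnancy test at the visit that section 6.9 already schedules for the day before clindamycin, with the result known before randomisation. Section 6.5 permits this order. State it in sections 6.2.1, 6.4 and 6.9, and add a pregnancy-test row to Table 1. As reproduced, Table 1 marks the start-of-treatment hospital visit under day 1, while section 6.9 puts it on the day before; align the two when adding the row.

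**Minor changes.**
- In section 6.2.2, state that the 3-month antibiotic window runs to the first clindamycin dose. Use the section 6.4.1 medication question at the day-before visit to confirm eligibility under section 6.5.
- Let the sponsor set a maximum age for the *C. difficile* result at first dose, with a repeat test beyond it, because section 3 relies on that result.

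**Cost.** Protocol wording and one urine test per woman at an existing visit: at most 24 tests if all 24 participants were women, plus any for replacements. The downside is an occasional late exclusion after stool has been donated and perhaps processed. Testing before randomisation keeps such an exclusion out of the randomised comparison. The repeat test narrows the risk but cannot remove it, since a very early pregnancy may still be undetectable.

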### 6.4.1 Prior and concomitant medications

Medication history (prior medications) is needed prior to study start. Prescription medications, over the- counter (OTC) medications, and herbal products will be asked for.

The Investigator or designee should assess changes in concomitant medications throughout the study by asking the subject at each visit. Any changes reported by the subject should be recorded in the e-CRF. Medications will be coded according to the World Health Organisation’s (WHO) Anatomic Therapeutic Chemical classification system (ATC) classification.

## 6.5 Randomization

Participants will be concurrently randomly allocated into two arms in a 1:1 fashion. Randomization is to be performed after eligibility has been confirmed and at least 1 hour prior to start of clindamycin treatment.

Patients who fulfil all the inclusion criteria and none of the exclusion criteria are eligible for inclusion into the study and will be randomised into two arms:

- Group A: Clindamycin + Capsules with faeces solution
- Group B: Clindamycin + Placebo Capsules

Randomization is performed centrally.

## 6.6 Blinding

Identical capsules will be given to the subjects. After randomization, the two groups of subjects are followed in exactly the same way. Treatment code envelopes will be provided for each randomised subject.

### 6.6.1 Breaking the treatment code (un-blinding)

Treatment code envelopes will be provided for each randomised subject. The code envelopes will be kept in a secure place with limited access. In case of such emergency that it is crucial for the Investigator, or any other treating physician, to know whether the subject has received study product or placebo, the code envelope may be opened. If the code is broken, this must be documented on the treatment code envelope and in the subject’s hospital records with date and name of the Investigator who decided to break the code.

In the event of an SAE, the Investigator may only break the treatment code if the appropriate future management of the subject necessitates knowledge of the current treatment. Although it is advantageous to retain the blind for all subjects prior to final study analysis, when a SAE may be a serious adverse reaction unexpected or otherwise judged reportable on an expedited basis, it is recommended that the blind should be broken only for that specific subject, by the sponsor, even if the Investigator has not broken the blinding.

The treatment code will not be broken until all assessments have been performed, all data have been entered into the database and the database has been locked after a formal clean file has been produced. The safety committee will monitor data in a blinded fashion during the study.

## 6.7 Subject withdrawal

Subjects are free to discontinue their participation in the study at any time and for whatever reason without affecting their right to an appropriate follow-up investigation. If possible, the reason for withdrawal of consent should be documented.

Once a subject has been included in the study, the Investigator should make every reasonable effort to keep the subject in the study.

Subjects may be discontinued from the study at any time at the discretion of the Investigator. Specific reasons for discontinuing a subject from further assessments are:

- Withdrawal of informed consent
- Subject lost to follow-up (i.e. drop-outs)
- Death
- Substantial Clinical Study Protocol violation
- The Investigator’s decision

The Investigator will make every reasonable effort to complete the procedures outlined for the end of treatment visit for subjects who have received study medication and are subsequently withdrawn from the study.

##

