## 7.8 Stopping rules

If an attending physician assesses that a patient is suffering from an adverse event induced by the IMP and requiring treatment, IMP treatment will be stopped for that patient. The outcome will be classified as an adverse event necessitating treatment stop. Should a study participant develop CDI this will be treated as per routine with metronidazole and in case of recurrence with autologous faecal transplant as per routine.

The data and safety monitoring board and the Swedish Medical Products Agency have the right to stop the study.

A study subject can terminate his/her participation in the study at any time without giving a reason why as outlined in patient information (appendix C). Should a subject wish to do so he/she will be treated in line with standard recommendations.

Study organisers can end a patient’s participation for safety reasons.

If a patient is excluded, already collected data will be used in subsequent analyses unless he/she objects.

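### Section 6.7 lets a protocol violation or the Investigator's decision end all further assessments, not only capsule intake, before the 21-day primary safety window has closed

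*Protocol*

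**What the plan says.** Section 6.7 gives the Investigator open discretion: "Subjects may be discontinued from the study at any time at the discretion of the Investigator". It then lists what it calls "Specific reasons for discontinuing a subject from further assessments are": withdrawn consent, loss to follow-up, death, "Substantial Clinical Study Protocol violation", and the Investigator's decision. The violation is not defined. The same section says that "the Investigator should make every reasonable effort to keep the subject in the study", and that for treated participants who are then withdrawn an effort will be made to "complete the procedures outlined for the end of treatment visit".

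Section 7.8 treats one group separately. Where a physician judges that the study product has induced an adverse event "requiring treatment, IMP treatment will be stopped for that patient", and the stop is itself classified as an outcome. The section also allows the organisers to end participation for safety reasons and does not say whether assessments then continue. On data in hand it states: "If a patient is excluded, already collected data will be used in subsequent analyses unless he/she objects".

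The primary endpoint (5.1) is safety and tolerability up to 21 days after the end of faecal treatment. Section 7.6 has all adverse events followed to resolution or the end of follow-up, with reporting to 6 months after the study product.

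**The concern.** Three of the five reasons in 6.7 (withdrawn consent, loss to follow-up, death) make further assessment impossible or unauthorised. The other two do not. A participant withdrawn for a violation or by the Investigator's decision can still be reached and has not refused, yet the text lets assessment stop by choice.

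This matters because safety and tolerability are the primary endpoint. Under section 6.9 only the first dose is supervised, and the rest are taken at home. Missed doses are a foreseeable deviation, and mild nausea or disgust is a foreseeable reason for them. If some of those participants are judged to have violated the protocol substantially, the missing follow-up is related to the outcome being measured. The microbiota and stool-habit endpoints would lose the same people. A statistical analysis plan can choose how to handle missing data, but it cannot supply observations that the protocol allowed not to be collected.

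**Working it through.** The protocol gives no power, event rate or dropout figure (section 11.1), so there is no stated number to reproduce. The check compares what 6.7 secures with what the endpoints need, then sizes the gap.

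**Timing** (5.1, 6.10, 7.6, Table 1)
- Treatment occupies days 10 to 15, so the primary window closes at about day 15 + 21 = day 36.
- Table 1 labels no end of treatment visit. The nearest is the hospital visit on day 16.
- Primary window left uncovered after that visit: 36 − 16 = 20 days. Adverse event reporting under 7.6 runs far beyond it, to 6 months.
- The CRF B questionnaire is daily to day 28. For someone withdrawn on day 11, 28 − 11 = 17 daily records remain, and an attempted day 16 visit would recover little of that.
- Four stool samples are scheduled after treatment (day 16, day 28, 2 months, 6 months). Three of them fall after the day 16 visit.

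**Exposure to the rule** (6.9)
- Twice daily for five days is 2 × 5 = 10 doses. One is supervised, leaving 9 unsupervised.

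**Weight of one participant** (11.1)
- With 12 per arm, 1/12 = 8.3 percentage points.

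**Loss of information if withdrawn participants contributed nothing** (assumed 2 or 3 lost from one arm)
- Two-sided 95% upper limit after zero events, 1 − 0.025^(1/n): 26.5% for 0/12, 30.8% for 0/10, 33.6% for 0/9.
- Chance of seeing at least one event at an assumed true rate of 10%, 1 − 0.9^n: 71.8% for n = 12, 65.1% for n = 10, 61.3% for n = 9.
- These are outer bounds, because 7.8 keeps what was recorded before withdrawal. They apply in full only to events that first arise afterwards.

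**The sections side by side**
- 6.7 allows assessments to end, while 7.6 says every adverse event is followed and the reporting period runs to 6 months. No sentence says which prevails.
- 7.8 separates stopping the product from leaving the study, but only for a product-induced event that requires treatment. Milder intolerance leading to skipped doses is outside that sentence.
- The provision on collected data in 7.8 protects past observations and does not require new ones.

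**The case against.** The protocol has real safeguards. Collected data are used, and daily questionnaires capture symptoms before any withdrawal. A product-induced stop is counted as an outcome, and adverse events are to be followed to resolution or the end of follow-up. Retention is urged, and section 11.3 reports the proportion withdrawn or lost. The clause in 6.7 is permissive, the violation must be substantial, and section 8.6 has individual deviations recorded with a reason, without requiring removal. Investigators are blinded, so they cannot knowingly favour an arm.

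Most of this stands, and it rules out several stronger readings:

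- A reader might infer that the rule deletes tolerability outcomes. Section 7.8 contradicts that for anything already recorded.
- A reader might infer that the people removed are precisely those who do not tolerate the capsules. Section 6.7 names neither intolerance nor an adverse event as a reason, so the overlap is possible but not prescribed.
- A reader might count rescue medication as a violation. No list of prohibited drugs exists; section 6.4.1 only records changes in medication.
- A reader might illustrate the harm as 3/12 (25%) becoming (3 − 2)/(12 − 2) = 1/10 (10%). That needs two events to arise after removal and the two participants to leave the denominator, and no section prescribes the second step. If intolerance prompted the removal, the event came first and is kept.

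The safeguards do not close the remaining gap. None of them clearly requires assessment through the primary window after a withdrawal for violation or by the Investigator. Reporting the proportion withdrawn shows the loss without recovering the data. Blinding prevents deliberate selection by arm, but not selection through symptoms if these differ between arms. Which participants enter the analysis is commonly left to the statistical analysis plan and is not part of this point.

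**Conclusion.** The point holds as a narrow but genuine gap. Section 6.7 merges stopping treatment with stopping assessment for two reasons that do not require it, and section 7.8 leaves the same question open for removal on safety grounds. Followed as written, about 20 days of the primary window (day 16 to about day 36) and most of the 6-month follow-up may go unobserved in consenting participants, possibly for reasons related to tolerability.

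How many participants this would affect cannot be derived from the protocol. Each one is 8.3 percentage points of an arm, and only events first arising after withdrawal are at risk. The conclusion assumes that treatment ends on day 15 and that the day 16 visit is the one meant by the end of treatment visit. The correction is worth making because later analysis cannot repair the loss.

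**What to change.** Reconcile section 6.7 with 7.6 and 7.8:

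- State separately what stops study capsules and what ends follow-up.
- Let only withdrawal of consent, loss to follow-up or death end assessments.
- After any other stop, including one under the safety sentence in 7.8, continue CRF B, adverse event reporting and scheduled stool samples as planned, at least through the 21-day primary window and preferably to 6 months.
- Say which visit in Table 1 is the end of treatment visit.

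The criteria for stopping treatment are left as they are. The cost is a wording change in two sections, a label in Table 1, and continued questionnaires and samples for the few who stop early.
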